**Fig. 1 Fig1:**
[figure not shown]
Study Design Flowchart

### Study setting and participant recruitment

This research will take place in Surabaya, Indonesia, a modern industrial city located on the northern shore of eastern Java. Surabaya is the second largest city in Indonesia and is home to approximately 2.9 million people in 2020 (85% majority Muslim, primarily Javanese). Notably, Java is Indonesia’s most populated island, home to approximately 56.1% of the population, and the Javanese people form the largest ethnic group in Indonesia [57].

Study participants will be 2000 Indonesian adolescents attending junior high schools in grades 7–9, alongside approximately 20–30 teachers and/or school guidance counsellors. Once permission to carry out this research has been obtained from the Surabaya District Education Office, junior high schools throughout Surabaya will be invited to participate based on the study eligibility criteria. School recruitment will be supported by UNICEF Indonesia. Eligibility criteria for schools and students can be seen in Table 4. Eligibility will be confirmed during the school recruitment process.

**Table 4 Tab4:** Participation Eligibility Criteria at the School and Student Level

Inclusion Criteria	Exclusion Criteria
**School Eligibility Criteria**	
Co-educational state junior high schools (overseen by the Ministry of Education and Culture).	Madrasas (i.e., Islamic schools. Madrasas can be public or private. Public Madrasas are overseen by the Ministry of Religion). Private schools.
Have prior experience in delivering online instruction via video-conferencing platforms.^a^	Have delivered dedicated lessons on body image to current grade 7–9 students in the past year.
	Have taken part in UNICEF Indonesia’s LSE in the past year.
**Student Eligibility Criteria**	
Adequate literacy levels in Bahasa Indonesia (as determined by their teacher) to ensure students are able to independently read project materials.	^a^No access to an electronic device with an internet connection (e.g., tablet, laptop, desktop computer).
In grade 7–9.	

^a^criterion added due to COVID-19 pandemic restrictions

Teachers who are trained in delivering the body image lesson will identify students for the study using the eligibility criteria in Table 4. The teacher will send an electronic copy of the study information and consent letters to eligible students’ parent(s)/guardian(s). Active parental consent is a requirement from the Universitas Indonesia for young people under the age of 18. The information letter will detail the purpose and design of the trial, the risks and benefits to their child, how their child will be involved, how information will be stored, and ethical approval details. Parent(s)/guardian(s) will be given time to consider the information; the information sheet will provide contact details for members of the research team in Indonesia (authors BEM and KN) whom they can contact if they have any questions or queries at any point in the trial. Parent(s)/guardian(s) will be asked to confirm they have had the opportunity to read the information sheet provided and ask any questions. They will be asked to give their full name and consent for their child to take part in the research study. Parents are also asked to provide the full name of the child, so researchers can confirm consent with participant attendance at the teaching session and data collection time points. An example parent information and consent form is presented in Additional file 2. Informed parent consent will be provided electronically to the child’s teacher, who will pass this information to Cimigo. In addition, informed active assent will be electronically obtained from all students and matched with parent consent prior to data collection.

### Measures

Self-report measures to assess study outcomes were selected based on their use with adolescents in multiple studies internationally and are consistent with the *Dove Confident Me: Single Session* UK trial [37] to allow for comparison in outcomes.

However, to date, there are no existing validated measures of the outcome variables for use with adolescents in Bahasa Indonesia among Indonesian adolescents. Authors KMG, NC, SH, PCD, KN, BEM, and LAS are currently psychometrically validating the measures selected for the trial based on self-report data from Indonesian adolescents in Surabaya and Greater Jakarta, following a process outlined by Swami and Barron [58]. In brief, items from each measure were first analysed for cultural suitability by an expert Indonesian panel. Next, items were forward translated to Bahasa Indonesia by two independent translators fluent in both English and Bahasa Indonesia (their first language is Bahasa Indonesia) and back translated to English by a further two bilingual translators. Resulting translations from both rounds were reviewed by authors fluent in Bahasa Indonesia (LAS, KN, and CR), and any discrepancies in translations were subsequently resolved.

Next, acceptability interviews with 18 private and state school students aged 12–15 years were conducted by CR in Greater Jakarta, which provided support that the translated measures are likely to be understood and age-appropriate for Indonesian adolescents. Data has been collected from over 1000 Indonesian adolescents who completed the adapted and translated measures. Data is currently been prepared for analysis to assess the psychometric properties, reliability, and validity of each measure in this context, which will be completed prior to the analysis of the main trial. This research will be published in international peer review journals, with the findings informing how the measures will be utilised for purposes of the current trial.

#### Primary outcome measure: Body esteem

The primary study outcome will be body esteem, a specific component of body image, defined as a person’s self-evaluation of one’s body or appearance [59]. Body esteem will be measured using a culturally adapted Bahasa Indonesia version of the Body Esteem Scale for Adolescents and Adults (BESAA) [59]. Specific items and subscales to be used during the analyses will depend on the findings of the psychometric testing of the measure, as previously described. The self-report items are rated on a five-point Likert-type scale from 1 (never) to 5 (always). Negatively worded items are reverse scored and higher mean scores indicate greater body esteem.

#### Secondary outcome measures

Mood will be assessed using a culturally adapted Bahasa Indonesia version of the Positive and Negative Affect Schedule for Children (PANAS-C) [60]. Participants will rate one-word descriptors of positive affect (e.g., “cheerful”) and negative affect (e.g., “miserable”) on a five-point Likert-type scale from 1 (never) to 5 (always). Scores of positive items and negative items will be averaged as separate subscales so that higher mean scores of the positive items indicate greater positive affect and higher mean scores of the negative items indicate greater negative affect. As described, the specific number of items that will make up each subscale is currently unknown.

Internalisation of societal appearance ideals will be assessed using a culturally adapted Bahasa Indonesia version of the internalisation-general subscale of the Sociocultural Attitudes Towards Appearance Questionnaire-3 (SATAQ-3) [61]. Participants will be asked to indicate agreement with items (e.g., “I wish I looked like the models in music videos”) on a five-point Likert-type scale from 1 (totally disagree) to 5 (totally agree). Higher mean scores indicate greater internalisation of societal appearance ideals.

Reduced life engagement related to negative body image will be measured using a culturally adapted Bahasa Indonesia version of the Body Image Life Disengagement Questionnaire (BILD-Q) [62]. Participants will be asked to indicate the frequency with which they have not participated in an activity (e.g., giving an opinion, going to the doctor) due to worrying about their appearance by using a four-point Likert-type scale from 1 (not at all) to 4 (all the time), with higher mean scores showing poorer life engagement due to negative body image.

A purpose-built skin shade chart will be used to assess change in skin shade satisfaction. The chart will comprise of nine skin colours (using colours from The Pantone Skin Tone Guide: www.pantone.com/) from dark (1) to light (9).^4^ Participants will be asked to indicate which skin shade best represents their “current skin shade” and which best represents the skin shade they would like to have – their “ideal skin shade”. This will allow for a current ideal skin shade discrepancy score to be calculated as an indicator for skin shade satisfaction. As this measure has not yet been utilised among Indonesian adolescents, two further items will be included to assess the validity of this measure. The first additional item (i.e., “How dissatisfied or satisfied are you with the colour of your skin?”) provides response options on a five-point Likert-type scale 1 (very dissatisfied) to 5 (very satisfied). The second item (i.e., “Which of the following statements do you agree with the most?”) offers the following response options on a three-point Likert-type scale: “I would like my skin colour to be lighter”; “I would like my skin colour to stay the same”; and “I would like my skin colour to be darker”. These items will be corroborated with the current ideal discrepancy scores; provided there is a good correlation among scores, the current ideal discrepancy score will be used as the outcome variable on skin shade.

Finally, two purpose-built items will be included to assess the change in participants’ tendency to engage in appearance comparisons in the past week (i.e., “I compare my appearance to celebrities and influencers” and “I compare my appearance to people my age”). The two items will be rated on a five-point Likert-type scale 1 (never) to 5 (always). Provided there is good internal reliability between the two items [63], scores will be averaged, with higher mean scores indicating a greater tendency to engage in appearance comparisons.

#### Demographic information

At baseline (T1), participants will be asked to self-report demographic information (i.e., age, gender, ethnicity, and religion), in addition to their height and weight (if known) to calculate their body mass index (BMI).

### Intervention acceptability

Quantitative and qualitative intervention acceptability data will be collected from students and teachers in the intervention condition. Acceptability questions, adapted from the *Dove Confident Me: Single Session* UK trial [36] will be incorporated into the post-intervention (T2) assessment survey. First, students will be asked to rate the lesson using a five-point Likert-type scale from 1 (strongly disagree) to 5 (strongly agree) on perceived enjoyment, helpfulness, understanding, comfort, teacher competence, topic importance, the likelihood to take future action to improve body confidence in themselves or others, and whether they will recommend the lesson to a friend. Second, students will be invited to provide free-text responses on what they liked most and least about the lesson, as well as their preference regarding the number of body image lessons using a three-point Likert-type scale (i.e., “I would like more sessions on body image”; “I think one session on body image is enough”; and “I think we do not need any sessions on body image”). Third, they will be asked what they perceived as the key messages of the programme via a free-text response to assess whether the learning objectives were understood. Fourth, students will be asked to rate the acceptability of the online delivery format of the lesson on a three-point Likert-type scale (i.e., “I had a good connection”, “My connection was okay”, and “I had a poor connection”). Finally, a free-text option will also be provided to describe any connectivity issues they might have experienced.

Teachers delivering the lesson will be asked to complete a short acceptability questionnaire online to capture their perspective of the programme in terms of the relevance of the topic for their students, adherence to the content, student engagement, and perceived student understanding. Then, in-depth acceptability data will be obtained from a subset of students (approximately *n* = 16) in a series of single-gender online focus groups (2 x focus groups with girls; 2 x focus groups with boys) led by a trained researcher. Similarly, a subset of teachers (approximately *n* = 6) will participate in an online acceptability focus group. Schedules for both the student and teacher focus groups are presented in Additional file 3: Acceptability Focus Group Schedules.

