### Paper and study aims

This paper aims to describe how *Dove Confident Me Indonesia: Single Session* was culturally adapted for use in Indonesian junior high state schools. It details the methods that will be employed to evaluate the intervention’s effectiveness and acceptability in a randomised controlled trial, as well as considerations for conducting this research during the COVID-19 pandemic. It also provides the plan for dissemination and highlights the strengths and limitations of the research trial study design.

The aim of the study outlined in this paper is to evaluate *Dove Confident Me Indonesia: Single Session*, as delivered online to students by schoolteachers or school guidance counsellors working in Indonesian state schools, in terms of intervention effectiveness and acceptability. Although originally designed to be delivered in a face-to-face format in school classrooms, project partners made a collaborative decision to evaluate the effectiveness of the intervention delivered in an online setting (i.e., via virtual video-conferencing classrooms) in response to the ongoing COVID-19 pandemic.^2^ Considering this adaptation, this study aims to assess the acceptability of the curriculum and pedagogy with students and teachers as well as the programme’s effectiveness in improving body esteem and related psychosocial outcomes. In line with previous evaluations of single-session body image interventions [36], we anticipate the intervention to provide short-term (up to two months follow-up) improvements in body image compared to a wait-list control group in order to assess the absolute impact of the intervention. Moreover, in line with the Tripartite Influence Model [51] and the targeted risk factors *Dove Confident Me Indonesia: Single-Session* aims to address, we anticipate a short-term reduction in internalisation of appearance ideals and appearance comparisons, alongside a reduction in the extent to which negative body image prevents adolescents from engaging in life activities relative to the wait-list control group. Finally, due to cultural adaptations of the original programme to challenge harmful skin shade ideals in Indonesia, we anticipate short-term improvements in skin shade satisfaction.

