### Internal pragmatic pilot study

Before commencing with the main cluster RCT evaluation, we will conduct a pragmatic internal pilot to assess the feasibility of recruiting and retaining participants to the online trial, as well as assessing preliminary acceptability of the intervention. The pilot will be conducted with two schools, with two classes per school (grades 7 and 8). The schools will be randomly allocated to either the intervention or wait-list control group. We expect approximately 60 students to participate per school, a sufficient sample size for testing the feasibility of a trial [54]. The pilot consent process will be the same as is detailed for the main trial. Two teachers or school guidance counsellors at the intervention condition pilot school will be trained to deliver the lesson by a member of the research team (CR). They will also be asked to complete the body image component of the UNICEF LSE teacher training e-module as previously detailed.

Participating students in the intervention condition school will take part in the *Dove Confident Me Indonesia: Single Session* lesson facilitated by one of the trained teachers with their class peers (up to 30 students per group) via a video-conferencing platform. They will complete the online survey assessment three times in line with the main trial timings: One week prior to the lesson (T1), 1 week after the lesson (T2), and 8 weeks after the lesson (T3). Lesson fidelity will be assessed by trained members of Cimigo, the local research agency conducting the research, following a checklist as well as a member of the research team (KN). Students in the intervention condition will also be asked to provide feedback on the acceptability of the lesson as well as the experience of participating in the lesson (including the use of breakout rooms) at the end of the T2 online survey. Further, two focus group discussions with students took part in the lesson (one group of girls, one group of boys) and two individual interviews with the teachers who delivered the lesson will be held to gather insights on the acceptability of the lesson. Participating students in the wait-list control condition will complete the three online survey assessments in parallel with the intervention condition (T1, T2, and T3). The school allocated to the wait-list control will be provided with lesson materials following T3. Feasibility feedback on the research procedure will be collected from Cimigo.

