### Limitations

We acknowledge several potential study limitations. We transitioned this research and intervention delivery to an online modality in response to the ongoing COVID-19 pandemic and related restrictions. This means that our eligibility criteria are now limited to higher-income schools and participants than previously intended, as it is essential students and teachers are experienced in live online teaching via video-conferencing technology and that students have access to their own electronic device. This is not representative of all students attending state junior high schools across Indonesia. For example, according to internal monitoring reports at the start of the COVID-19 pandemic by the Basic Education Working Group [70], less than 20% of teachers surveyed reported using interactive video conferencing technology, such as Zoom or Google Meet, and only 25% of children living in urban areas have computers to use for home-based learning. While the government has since made efforts to provide data packages for students’ education, many students remain without access to digital devices. Nonetheless, an online delivery modality will circumvent ethical and safety risks associated with attempting to run a face-to-face intervention during the COVID-19 pandemic and will offer new insights into the delivery of online mental health interventions delivered by teachers more broadly.

Given Indonesia’s diversity, a related limitation is that results from the trial may not be generalisable to adolescents across Indonesia as we are only evaluating the lesson in a single city (i.e., Surabaya). However, preliminary field testing of the intervention topics and activities with teachers and adolescents was conducted in two provinces reflecting different majority ethnic groups and religion (West Papua and South Sulawesi) prior to finalising the intervention content, in addition to focus groups on topic content with adolescent girls in Greater Jakarta. Further, the Ministry of Education and Culture reviewed the intervention content prior to it being finalised for testing, and this review process included teachers, officials, and experts from across the country.

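### The one main-trial survey item labelled as a rating of online-format acceptability measures internet connection quality, so the survey has no direct rating of the format (minor point)

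*Protocol article*

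**What the plan says.** The Intervention acceptability section of the protocol article lists what intervention-arm students are asked in the T2 survey.

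- **Lesson ratings.** "students will be asked to rate the lesson using a five-point Likert-type scale from 1 (strongly disagree) to 5 (strongly agree"). Eight topics are named: enjoyment, helpfulness, understanding, comfort, teacher competence, importance of the topic, likely future action, and recommending the lesson to a friend.
- **Open comments.** "students will be invited to provide free-text responses on what they liked most and least about the lesson". Students also state how many body image lessons they would want and what they took the key messages to be.
- **Online format.** "students will be asked to rate the acceptability of the online delivery format of the lesson on a three-point Likert-type scale". The options given are "I had a good connection”, “My connection was okay”, and “I had a poor connection".
- **Follow-up free text.** "a free-text option will also be provided to describe any connectivity issues they might have experienced".

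Outside the survey, the section plans four single-gender student focus groups (about 16 students in all), a teacher questionnaire and a teacher focus group.

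The section Paper and study aims explains that the lesson was designed for the classroom and moved online because of the pandemic. In light of that change, "this study aims to assess the acceptability of the curriculum and pedagogy with students and teachers". The Limitations section adds that online delivery "will offer new insights into the delivery of online mental health interventions delivered by teachers more broadly".

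**The concern.** The label and the content of the format item do not agree. The label names a judgement by the student: was online delivery acceptable? The options record a circumstance: how well did the internet connection work? The two can part company in either direction. A student with a flawless connection may have disliked talking about appearance in an online group, yet would give the best answer on this item. A student who was glad to have the lesson online but had a weak signal would give the worst.

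Acceptability is a stated aim, and the protocol introduces it in the context of the move online. If the item is summarised under its present label, connection quality will stand in for acceptability of the format. That matters for how far results from this online delivery can inform online teaching elsewhere, or the classroom lesson for which the material was written.

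**Working it through.** No arithmetic applies. The check has two steps: compare the item's label with its content, then look for any other student measure of the format.

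**Step 1: label against content** (Intervention acceptability)

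| Element | What it covers |
|---|---|
| Stated construct | Acceptability of online delivery |
| Response options | Good, okay or poor connection |
| Paired free text | Connectivity problems |

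The options are introduced with i.e. and not e.g., so they are presented as the whole scale and not as an illustration. Neither the options nor the free text asks for an opinion of the format.

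**Step 2: other student evidence on the format**

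| Source | Section | Bearing on the format |
|---|---|---|
| Eight five-point ratings | Intervention acceptability | Indirect. They rate a lesson given only online, so format affects them, but no item separates it from content or teacher. |
| Liked most and least | Intervention acceptability | Possible but unprompted. |
| Preferred number of lessons; key messages | Intervention acceptability | None specific to the format. |
| Student focus groups | Intervention acceptability | Possible and qualitative. The schedules are in an additional file that is not shown. |
| Pilot T2 survey | Internal pragmatic pilot study | Direct, but pilot only. Students give feedback on "the experience of participating in the lesson (including the use of breakout rooms) at the end of the T2 online survey". |
| Pilot progression criteria | Table 3 | Pilot only. Adherence is read together with qualitative comments on online delivery. |

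Other process data do not supply a student rating of the format either. The teacher questionnaire covers relevance, adherence, engagement and perceived understanding. The fidelity assessors note technological difficulties (Intervention fidelity).

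The lesson ratings cannot be broken down further by analysis. Every intervention lesson is delivered by video-conference and the control arm receives no lesson before T3, so no contrast in the data would separate format from content.

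**Result.** The main-trial survey, as described, contains one format-specific closed item. It measures connection quality. The number of closed items that directly rate acceptability of the format is zero.

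**The case against.** A reader might infer that the survey cannot show anything about whether students accepted online delivery. The documents do not support that. The lesson was given only online, so ratings of enjoyment, comfort and recommending it are ratings of an online lesson. A student uneasy about taking part by video could well mark the comfort item down, or say so under what was liked least. The focus groups can take up the subject, and their small number is no argument against them, because qualitative groups are not meant to represent a proportion of the arm. The pilot asks directly about the experience of taking part and can lead to changes in delivery before the main trial.

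It is also fair to say that the aim refers to curriculum and pedagogy, that no separate endpoint for format acceptability is defined, and that the remark about new insights in Limitations is not an objective. Nor does the protocol say how the item will be reported. With the options printed beside the label, a careful reader can see what was asked.

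All of this narrows the point, and it keeps the point minor. It does not remove the mismatch. The item, its label and its options are all printed in the article, so this is not detail left to a fuller document. The alternative sources are either mixed with content, unprompted, qualitative or confined to the pilot.

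**Conclusion.** The point holds in a limited form. The only format-specific student rating in the main-trial T2 survey carries a label that its content does not support, and the survey gives no direct quantitative measure of online-format acceptability. Evidence on the format will be indirect.

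The mismatch affects one item, to be put to an intervention arm planned at about 1000 students. It has no bearing on body esteem, the secondary outcomes, the sample size or the error rates.

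The conclusion assumes that the article lists the T2 acceptability content completely. If the full questionnaire has a further item on the online format, only the label needs correcting. What the focus-group schedules ask cannot be judged from the article, and nothing is claimed about them.

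**What to change.** 1. Rename the existing item as connection quality, treat it as a process measure, and do not report it as acceptability. It is worth keeping: it can help in interpreting the lesson ratings.
2. Add one or two items to the intervention-arm T2 survey on the existing 1 to 5 agreement scale that ask about the format itself. One could ask whether the student liked having the lesson online; the other, whether the student felt comfortable taking part in the online group activities. Report these as acceptability of the online format.

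The cost is under a minute of extra survey time plus translation into Bahasa Indonesia. The Procedure section places acceptability feedback at the end of the T2 assessment, so the new items would follow the outcome measures at that visit. If the survey can no longer be changed, the relabelling alone costs nothing and removes the error. Format acceptability should then be described from the indirect sources and named as such.
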